### Survey administration

2.5.

The survey will be advertised in weekly rounds, 1 month prior to dissemination using affiliated society social media accounts and the Surgical Infection Research Network Twitter account (@SIRNglobal).

The survey will be disseminated worldwide, with an international SSC to establish a network of distribution. The committee has been involved in previous successful surveys and collaborative projects through the PIACO group, the Vascular Endovascular Research Network (VERN), James Lind Alliance (JLA) and ISWCAP surveys (20–23). The committee will also identify new routes of distribution within this project. The validated online survey will be distributed using an electronic link. Participants will receive an email via their affiliated membership organization, inviting them to take part and will include a direct link to the online survey. Following the invitation, surgeons will have 3 months to complete the survey, with reminders sent every 2 weeks. The survey will also be promoted via social media platforms, using the SIRN Twitter account in addition to affiliated organization accounts. The “prevent multiple submissions” option in Qualtrics will be enabled to prevent multiple participation of participants. A secondary IP address check will follow to ensure there are no remaining duplicate entries. No two entries from the same IP address will be allowed within 24 h. After the data collection window, the survey will lock out, preventing further responses. Participants will be offered an opportunity to win a £20 Amazon voucher as an incentive to participate in the survey. Survey items will not be randomized to improve participation, as the logical order of each survey section was unanimously agreed by the SSC to improve the response flow. Adaptive questioning will be used depending on the following questions from a response. The number of items and screens or pages on mobile and personal computers will be reported in the manuscript write-up.

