### Sample characteristics

2.4.

The survey will be sent out electronically to surgeons of any specialty and at all levels of training worldwide. This includes consultants, and surgical trainees (specialties registrars/residents). To be included in the study, surgeons must be currently practicing and be registered with the national surgical body/college/society. The validated online survey will be distributed through Qualtrics^XM^ for single-stage cluster sampling in addition to dissemination through social media, where snowballing may occur. Each network of distribution will provide a cluster, i.e., VERN for the vascular surgeons and PIACO group for general surgery. The study population will provide a representation of existing SSI preventative measures used worldwide.

Given the global nature of the survey, no sample size will be calculated. Raking will be used to assign weight values to each survey respondent in such a manner, that the weighted distribution of the sample is in very close agreement with two or more marginal control variables. Socio-economic (developing vs. developed countries) variables and surgical specialties will be used to weigh the sample of responses. As such, results will be able to be extrapolated into wider populations, irrespective of the distribution of responses received.

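### The 24-hour IP rule tests a network rather than a person: it can discard genuine colleagues on a shared address and cannot deliver the promised absence of remaining duplicates

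*Protocol article*

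**What the plan says.** Section 2.5 (Survey administration) describes two layers of duplicate control. The first is a platform setting: the multiple-submission "option in Qualtrics will be enabled to prevent multiple participation of participants". The second is introduced with a firm aim: "A secondary IP address check will follow to ensure there are no remaining duplicate entries". Its only stated criterion is "No two entries from the same IP address will be allowed within 24 h". The article names no exception for shared networks, no other identifier and no comparison of answers.

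The setting in which the rule operates is also described:

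- **Population** (2.4, Sample characteristics): "The survey will be sent out electronically to surgeons of any specialty and at all levels of training worldwide".
- **Invitation** (2.5): "Participants will receive an email via their affiliated membership organization, inviting them to take part and will include a direct link to the online survey".
- **Open routes** (2.4): the link is distributed "in addition to dissemination through social media, where snowballing may occur".
- **Window** (2.5): "surgeons will have 3 months to complete the survey, with reminders sent every 2 weeks".
- **Incentive** (2.5): "Participants will be offered an opportunity to win a £20 Amazon voucher as an incentive".

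**The concern.** The rule can err in both directions.

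**Too strict.** The survey is open to all specialties and grades, so several eligible surgeons may work in one hospital. If they reach the internet through one public address and two reply within 24 h, the rule keeps one and drops the other, although both are genuine. The more respondents share an address, the larger the share lost, so the loss is selective. The raking in section 2.4 weights on development status and specialty only. It cannot restore the balance between respondents on shared networks and the rest.

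**Too lax.** Collection runs for 3 months with fortnightly reminders. Someone who answers again at a later reminder is far outside the 24 h window, and someone who answers from another connection has a different address. The open link and prize draw give opportunity and some motive. Any repeat that survives both layers enters the chi-square tests named in the abstract as if it came from an independent respondent.

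**Working it through.** The article states no figure to reproduce: no expected number of duplicates and no sample size. The check is therefore logical, with an illustrative calculation to show scale.

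**Inputs from the protocol (2.5).** One entry per IP per 24 h; a 3-month window, taken as 91 days; reminders every 2 weeks. This gives contact days 0, 14, 28, 42, 56, 70 and 84: the invitation and 6 reminders, 7 contacts in all.

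**Assumptions not in the protocol.** *k* genuine respondents share one public IP. Each, with probability *s*, replies within 10 h of one of the 7 contacts chosen at random; otherwise the reply falls uniformly over the 91 days. All sharers are contacted on the same days. An entry is lost if it comes less than 24 h after the last accepted entry from that IP, and there is no retry.

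**Genuine entries lost (simulation, share of all entries from that IP).**

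| Sharers *k* | *s* = 0 | *s* = 0.5 | *s* = 0.8 |
|---|---|---|---|
| 2 | 1.0% | 2.5% | 4.9% |
| 5 | 4.3% | 9.5% | 17.4% |
| 10 | 9.0% | 18.9% | 33.0% |
| 20 | 17.3% | 32.2% | 51.1% |

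**Hand check for *k* = 2, *s* = 0.8.** One entry is lost if the two fall within a day of each other.

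- Both follow a contact, and it is the same one: 0.8² × 1/7 = 0.0914.
- One follows a contact and the other is uniform. The stretch of the window within a day of a reply is 2 days for six contacts and about 1.2 days for the first, which is cut off by the start of the window. The mean is (6 × 2 + 1.2)/7 ≈ 1.89 days. The term is 2 × 0.8 × 0.2 × 1.89/91 = 0.0066.
- Both are uniform: 0.2² × [1 − (90/91)²] = 0.04 × 0.0219 = 0.0009.

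The sum is 0.0989. One of two entries is lost, so the share is 0.0989/2 = 4.9%, as in the table.

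**Repeats caught by the IP rule alone.**

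- Two entries by one person from the same IP at random times in the window: 1 − (1 − 1/91)² = 0.0219, so about 2.2% are caught.
- First entry at one contact and repeat at a later one, each within 10 h: the gap is at least 14 days less 10 h, so none are caught.
- Repeat from another IP: none are caught, whatever the timing.

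**The case against.** **There is a first layer.** The IP check is expressly secondary. A reader might infer that anyone can re-enter once a day, roughly 90 times over the window. The document does not support that: the platform setting may stop many later repeats, and the article does not say how it works. The 2.2% and zero above apply only to repeats that have already got past it, and their number is unknown. What stands is that the second check exists for exactly those repeats, and for them its criterion is weak. The first layer also does nothing for colleagues wrongly dropped.

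**Shared addresses and same-day replies are assumed.** Invitations go through separate membership organizations, and no common mailing day is stated, so colleagues in different specialties need not be contacted together. Phones and home connections would spare genuine colleagues, just as they would let repeats through. If refusal happens at entry, a surgeon could return later; if the check is run after collection, as its description as a following step suggests, that chance is gone. All this stands, and it is why the size is given as a range.

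**A larger loss can be produced.** With 5 sharers each having a 40% chance of replying on one mailing day, 2.0 reply on average and 2.0 − (1 − 0.6⁵) = 1.08 are rejected, or 54% of that day's replies. The arithmetic is right, but it concentrates replies on a single day. In the table, even *s* = 0.8 puts only 0.8/7 = 11% on each contact day. As a share of all five replies it is 1.08/5 = 22%, above the whole 5-sharer range. It should not be quoted as typical.

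**Within-hospital variation is not an objective.** A reader might infer that the rule destroys the replies needed to study variation inside institutions. Section 2.1 lists barriers, variation within and between specialties, and financial and economic systems. Section 2.3 names no hospital identifier among the data items. Variation within a specialty can be seen across hospitals. That stronger harm is not supported.

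**Condensation.** Further handling may sit in a fuller document. The finding does not rest on an omission, however: the article states the rule and the result it is meant to secure, and the two do not fit.

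**Conclusion.** The point holds for the rule as written. An IP address and a 24 h clock cannot separate two colleagues from one person answering twice. The check can discard genuine respondents on shared networks, and it cannot secure the absence of remaining duplicates.

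The logic needs no assumptions beyond some address sharing and some repeats that pass the platform setting. The size does need them: about 1–5% of entries lost for 2 sharers, 4–17% for 5 and 9–33% for 10, as *s* runs from 0 to 0.8, and lower with private connections or retries. The document does not allow the overall loss, the number of surviving duplicates, or the direction and size of any bias in a survey estimate to be derived, so none is claimed. The impact is moderate and avoidable, and the rule should be changed before the survey opens.

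**What to change.** 1. Keep the platform's multiple-submission setting as the first layer.
2. Do not reject on IP alone. Treat a repeated IP as a flag over the full 3-month window.
3. Remove a flagged entry only if specialty, grade, country and financial system all match (items already collected under section 2.3) and there is further evidence of the same respondent: the same device cookie, or identical answers across the whole questionnaire including free text. Near-identical answers are not enough, because colleagues working under one hospital policy may answer alike.
4. Keep the first complete entry of a confirmed set.
5. Report the numbers flagged and removed, with a sensitivity analysis that retains all flagged entries.
6. In section 2.5, replace the claim to ensure that no duplicates remain with a claim to reduce them.

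Single-use links where a society can mail them, and a separate voucher form used to detect repeats, are optional additions. The cost is a platform setting, a short matching script and a modest manual check of flagged pairs. Repeats from a different address would still pass the IP flag, which is why the wording should change as well.

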### Objectives

2.1.

Primary objective:
-To identify the barriers to establishing standardized SSI prevention practice.Secondary objectives:
-To identify intra- and inter-specialty variations in surgical site infection prevention practice.-To identify variations in practice amongst financial systems such as state and privately funded healthcare systems and economical classifications.

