### Study design

2.2.

This is an international, pan-specialty, collaborative cross-sectional survey. A global panel of experts will form the study steering committee (SSC), providing a consensus-based approach to survey development, validation, and distribution. This study will be reported in line with the checklist for reporting of survey studies (CROSS) and the checklist for reporting results of internet E-surveys (CHERRIES) (16, 17). Ethical approval is provided by the Hull York Medical School Ethics Committee (REF22-23 10).

To collect data, the survey will be delivered electronically online using the Qualtrics^XM^ Platform™, Utah, USA. The format will be designed to include a combination of binary, Likert or multi-select. Free text comments will be used to collect further detail but will be kept to a minimum to help ensure good completion rates.

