### Questionnaire development

2.3.

A pilot questionnaire will be developed based on SSI prevention measures outlined in the CDC (2017), WHO (2018), NICE (2019), Wounds UK (2020) and the International Surgical Wound Complications Advisory Panel (ISWCAP) guidelines. Additionally, feedback from the survey of surgical site infection prevention practice in UK vascular surgery will be used to inform survey questions/design (12–14, 18, 19). Since the survey will be targeting participants across multiple specialties, it will only contain general prevention measures widely applicable. A draft survey will be provided in Supplementary Material 1.

The questionnaire will be structured into five sections; demographics, SSI surveillance, preoperative, peri-operative and postoperative SSI prevention domains. Data will be collected on participant surgical specialty, operative grade, country of practice and financial healthcare system of practice. SSI data will include criteria used for diagnosis. There were 15 perioperative domains formulated the UK questionnaire, which will be scrutinized against the CDC, WHO, NICE and ISWCAP guidelines outlined above by the SSC, to form a pilot questionnaire. The process of questionnaire development will be carried out through discussion by members of the SSC and a record of any question refinement will be documented. The number of questions will not be rigidly defined but the SSC will consider the impact on survey duration which can influence completion rates.

The pilot questionnaire will be distributed to at least two consultants of each surgical specialty; vascular, general, orthopedic and trauma, urology, plastic and reconstructive, cardiothoracic, neurosurgery and otolaryngology for multiple rounds of validation. After each round feedback will be analyzed by the SSC and consensus-based changes will be adopted. Any alterations will be done so on unanimous decision and documented as major (questions removed or added), and minor (wording alterations). The survey will be validated further in subsequent rounds until the SSC agrees no further alterations are required.

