### Limitations

3.1.

Reminders will be sent on a 2-weekly basis to increase the response rate and to prevent sampling bias. Additionally, the study will be advertised on its own Twitter account to gain attention. Response fatigue is a common issue, leaving some questions unanswered. To keep this to a minimum, the survey has been designed to only ask relevant questions and to be succinct, clear, and unambiguous.

Due to the nature of the study, there is room for responder and recall bias. To minimize this, questions wording and survey length have been considered carefully during all steps of the development of the survey. Questions will be categorized into SSI-related preoperative, perioperative, and postoperative themes to preserve the structure and enable ease of organization for respondents to follow.

Additionally, there may be discrepancies in the response rates between different countries, not providing an accurate representation of certain regions. There may also be different local/national guidelines and unequal access to certain resources depending on the geographical regions. As this survey will be delivered worldwide, questions are based on guidelines from the National Institute for Health and Care Excellence (NICE), Centers for Disease Control and Prevention (CDC) and World Health Organization (WHO). These guidelines are internationally recognized and available, therefore discrepancies between geographical regions and differences in local guidelines should be kept to a minimum.

There is no standardized consensus recommendation on SSI prevention regarding perioperative practice. Unsurprisingly this can lead to a discrepancy in clinical practice, as shown by a questionnaire study within the UK (15). If international and pan-surgical SSI prevention practices also vary, guidance recommended by international bodies is not being followed. This may be due to the lack of underlying evidence for SSI prevention practice, and thereby the necessity for high-quality RCTs to establish the best practice for patients and surgeons worldwide.

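### The rule against randomising survey items should not extend to unordered multi-select options, where one fixed order can shift the relative frequency of listed measures or barriers

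*Protocol article*

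**What the plan says.** Section 2.5 (Survey administration) of the protocol article fixes the order: "Survey items will not be randomized to improve participation, as the logical order of each survey section was unanimously agreed by the SSC". The stated purpose of the agreed order is flow; it was "unanimously agreed by the SSC to improve the response flow". The same section adds branching: "Adaptive questioning will be used depending on the following questions from a response".

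Section 2.2 (Study design) gives the answer formats: "The format will be designed to include a combination of binary, Likert or multi-select". Section 2.3 gives the layout: "The questionnaire will be structured into five sections; demographics, SSI surveillance, preoperative, peri-operative and postoperative SSI prevention domains". The three prevention sections therefore follow the patient through surgery, with the postoperative one listed last.

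Section 2.1 sets the primary objective, "To identify the barriers to establishing standardized SSI prevention practice", and among the secondary objectives, "To identify intra- and inter-specialty variations in surgical site infection prevention practice" and a comparison of financial systems. Section 2.4 adds that the sample will show which prevention measures are in use worldwide.

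Section 3.1 (Limitations) accepts that "Response fatigue is a common issue, leaving some questions unanswered", and relies on relevance, brevity, clear wording and thematic grouping to limit this. It does not mention the position of an item or an option.

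**The concern.** The rule against randomisation is stated for survey items in general, and the reason given is flow. Flow has no bearing on a list of options that has no natural order, such as a set of prevention measures or possible barriers. If everyone sees such a list in one order, any tendency to tick early options and pass over late ones acts on the same options for every respondent. The effect cannot then be separated from true use, and it cannot be recovered after data collection because display order never varied.

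At stake is the descriptive reading of the survey: which measures appear most used and, if barriers are asked as a list, which barriers stand out. The latter is the primary objective.

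**Working it through.** The plan has no figure to reproduce here, and it calculates no sample size. The check is to compare the reason with the rule, and then to see which results a position effect can reach.

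**1. Does the reason cover option order?** The phrase about the logical order of each section can be read in two ways.
- Sequence of the sections: this justifies a fixed section order and says nothing about what lies inside a section.
- Order of the questions within each section: this also justifies keeping questions along the care pathway in place.

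On neither reading does it give a reason to fix unordered options within one question. Rotating them leaves sections, questions and branching as agreed.

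**2. Comparing two options in one list.** Let both have true frequency p. Suppose position adds d to the first and takes d from the last. The reported gap is (p + d) − (p − d) = 2d, although the true gap is 0. The documents give no value of d, so these are assumptions:
- p = 40%, d = 2 points: 42% against 38%, a gap of 4 points.
- p = 40%, d = 5 points: 45% against 35%, a gap of 10 points.

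With random option order each option takes every position equally often in expectation, so both receive the same average shift and the expected gap is 0.

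**3. Level of one option.** A shift d common to all respondents moves its reported frequency by d.

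**4. Raking and sample size.** With weights w_g summing to 1 over groups g, the weighted estimate is Σ w_g(p_g + d) = Σ w_g p_g + d. The shift d passes through unchanged. More replies reduce the standard error but not d.

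**5. Comparing two groups on the same option.** This is what the secondary objectives ask for.
- Common additive shift: (p1 + d) − (p2 + d) = p1 − p2. If both groups are truly at 40% and d = 2 points, both report 42% and the difference stays 0.
- Common proportional loss f: (1 − f)p1 − (1 − f)p2 = (1 − f)(p1 − p2). A true difference shrinks, but none is created from nothing.

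A false difference between specialties or financial systems needs the order effect itself to differ between them. Branching makes this possible, because groups may reach a question after different numbers of earlier ones. Nothing in the article shows that it happens.

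**The case against.** The strongest reply is that the rule speaks of survey items, which most naturally means questions. The article never says how options are ordered. The draft questionnaire is assigned to Supplementary Material 1, which is not among the documents reviewed, and it would show how many unordered lists there are and whether barriers are asked as a list. This stands, and it is why the first step is to say what the rule covers. It does not remove the point, because nothing in the text exempts options from the rule.

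The fixed order is also deliberate, disclosed and reasoned. It follows the care pathway, supports branching and was agreed by the whole steering committee. This stands for sections and for stand-alone questions. Shuffling those would be a trade-off against a defensible choice and is not asked for.

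A reader might infer that order effects will be mistaken for differences in practice between specialties or financial systems. The documents do not support that: a shift common to all groups cancels or only attenuates in those contrasts.

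A reader might also want to express the harm as a rate of false positive tests between two listed options. The article plans no test of one measure against another. Both options would be answered by the same respondents, and the effect size and number of replies would all have to be assumed. Such a rate would say nothing about the planned analyses.

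**Conclusion.** The point holds in a limited form, and its severity is minor. Response flow does not justify a single fixed order for unordered multi-select options. If the rule is applied to them, comparisons between listed options can be shifted by up to 2d between first and last: 4 to 10 points under the assumed d of 2 to 5 points. The level of any one option can be shifted by d. Neither raking, nor more replies, nor the steps against fatigue in section 3.1 remove this.

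The conclusion rests on three assumptions: that the questionnaire contains unordered multi-select lists of measures or barriers, that the rule is taken to cover their options, and that some position effect exists. Its size in this survey is unknown.

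**What to change.** - Keep the agreed order of sections, of questions along the care pathway, of branching and of Likert scales.
- State in section 2.5 that the rule against randomisation does not cover options in unordered multi-select lists.
- Switch on random option order for those lists, with 'other' and 'none' fixed last, and export the display order with the responses.
- In section 3.1, name item position and fatigue in the later sections as a limitation whenever measures are compared with each other. Random option order does not cure late-section fatigue, because the sections stay fixed.

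The cost is a platform setting before launch, a documented steering committee decision, a larger export and slightly more reading effort for respondents.
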